### Strategies to improve adherence to interventions {11c}

Explain the details of the experiment to the patient when giving informed consent. Provide participants with an adequate understanding of the risks and benefits.The diagnosis must be correct for the subject under study.The prevention and treatment measures given should be effective and without serious adverse reactions.Patients who accept prevention and treatment measures must adhere to voluntary rather than forced.Patients fully understand the purpose and significance of treatment and actively accept effective treatment.Improve the quality of medical services and maintain a good relationship between researchers and participants to improve patient compliance.All the surgeons participating in the experiment signed relevant experimental agreements, including the Non-disclosure agreement, the standardized operation agreement according to the experimental scheme, and the agreement for truthful reporting of medical records. These strategies are supervised and implemented by the Ethics Committee.

### Relevant concomitant care permitted or prohibited during the trial {11d}

The similar type of surgery is prohibited during the trialOther complications arising from the procedure can be managed during the trial.Patients who drop out of the experiment during the course of the study will be no longer included in the analyses.Patients with other fatal complications will be no longer included in the analyses.All routine treatment procedures for women in care for low and medium rectal cancer, as deemed appropriate by the patient’s treating clinicians, will be permitted during the trial.Additional clinical review, further treatments, including treatment of rectovaginal fistula, and concomitant medications will be determined by clinical need and will be recorded in follow-up case report forms.

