### Criteria for discontinuing or modifying allocated interventions {11b}

The patient has complications before surgery.The patient agrees to the study but refuses to be randomly assigned.Conditions not suitable for the protocol are found during surgery. For example, during the surgical process, it is found that the patient does not have a suitable free fat flap with ovarian vascular pedicle available, or there is a need to change the surgical method or expand the surgical scope in crisis situations such as bleeding during the operation, or special circumstances with the location, size, and surrounding tissues discovered during the operation.The patient asks to be withdrawn from the protocol.The patient would be unable to continue the protocol due to other postoperative complications.Patients lost to follow-up.

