### Procedure for unblinding if needed {17b}

Not applicable. Because the researcher who is responsible for participant intervention will not turn a blind eye to the group assignment. Statisticians can be notified to delete data related to participants with a specific participant number.

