## Statistical methods

### Statistical methods for primary and secondary outcomes {20a}

The independent statistician is responsible for the statistical analysis with SPSS 24.0 software. Patient data that falls off will not be included in the analysis. In the statistical analysis, measurement data between the two groups will be analyzed with the *t*-test and rank-sum test, while categorical data will be analyzed with *χ*^2^ test. Data will be recorded as mean ± standard deviation or median (first quartile, third quartile). The experiment is a non-inferiority trial, and the statistical method is mainly based on “parameter estimation.” Using the primary endpoint, determine the confidence interval for the difference in the efficacy of surgical methods in preventing rectovaginal fistula between the control group and the cases group. The significance level used for statistical analysis will be two-sided with confidence intervals at the 95% level.

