### Methods in analysis to handle protocol non-adherence and any statistical methods to handle missing data {20c}

We perform statistical analysis on the complete case. The complete case is that all the data required for this study protocol are complete and there are no missing cases in order to be included in the final statistical analysis. The premise of this RCT is that it does not violate the treatment principles of the patient's disease and does not imply or modify the patient's treatment intention. The experiment respects the treatment willingness of each enrolled patient.

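### Randomised patients who drop out, have other fatal complications or have incomplete data leave the analysis, no all-randomised analysis is described, and one likely further exclusion can arise only in the experimental arm

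*Protocol article*

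**What the plan says.** Four places in the protocol article bear on who is analysed.

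- Section {11d} (concomitant care): "Patients who drop out of the experiment during the course of the study will be no longer included in the analyses" and "Patients with other fatal complications will be no longer included in the analyses".
- Section {20a} (statistical methods): "Patient data that falls off will not be included in the analysis".
- Section {20c} (non-adherence and missing data): "We perform statistical analysis on the complete case". It defines such a case as one with every item the protocol requires.
- Section {17b} (unblinding): "Statisticians can be notified to delete data related to participants with a specific participant number". It does not say who asks for this or on what ground.

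Section {11b} lists criteria for discontinuing or modifying the allocated intervention. One example is that at operation "it is found that the patient does not have a suitable free fat flap with ovarian vascular pedicle available". Others are bleeding or a change of surgical method, withdrawal, loss to follow-up, and: "The patient would be unable to continue the protocol due to other postoperative complications".

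The flap step belongs to the experimental operation only ({6b} and {11a}). The surgeon opens the allocation envelope in order to perform the corresponding operation ({16c}). Sections {8}, {14} and {20a} frame the trial as non-inferiority. Nowhere is an analysis of all randomised patients in their allocated arm described.

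**The concern.** Randomisation makes the arms comparable only as long as the patients randomised are the patients compared. Here patients leave the comparison because of events after allocation, and some of those events are plausibly linked to the outcome. A patient who cannot continue because of a postoperative complication, or who has a fatal one, may be a patient whose anastomosis failed, and that is close to the process that produces a rectovaginal fistula (RVF).

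One criterion is also lopsided. An unusable flap is discovered only when a flap is sought, by a surgeon who knows the arm. Control patients with the same anatomy are never identified and stay in.

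The complete-case rule widens the loss. Table 1 schedules eleven follow-up visits from month 3 to month 60, with hormones, tumour markers and quality of life at each. Read literally, one missed blood test removes a patient whose RVF status is known.

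At stake are the validity of the primary comparison and part of the feasibility aim in section {7}, since the share of patients in whom the flap cannot be made is itself a feasibility result.

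**Working it through.** **1. The plan's own loss figure.** Section {14} gives 115 per group, 20% loss and 144 to be enrolled. 115 / (1 - 0.20) = 143.75, rounded up to 144, so the inflation step reproduces. The 115 itself does not reproduce per group from 9.9% in both arms, a 15-point margin and 80% power: the unpooled formula gives 63 per arm at one-sided 0.025 and 50 at one-sided 0.05. That is a separate matter. The 115 is taken as given here.

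**2. Losses against events.** The text does not say whether 144 is per group or in total.

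| Reading | Randomised per arm | Removed per arm | Expected RVFs among those kept |
|---|---|---|---|
| 144 per group | 144 | 144 - 115 = 29 | 115 × 0.099 = 11.4 |
| 144 in total | 72 | 72 × 0.20 = 14.4 | 57.6 × 0.099 = 5.7 |

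On either reading, removed patients outnumber events by about 2.5 to 1.

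**3. How much the removed patients could matter.** Take 144 per group and suppose a proportion e of the 29 removed would have had an RVF (e is assumed). The risk in the full arm is (11.385 + 29e) / 144:

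- e = 0: 7.9%
- e = 0.10: 9.9%
- e = 0.25: 12.9%
- e = 0.50: 18.0%

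**4. The flap criterion, with no true flap effect.** Let f be the share of the experimental arm without a usable flap and RR their RVF risk relative to patients with one. The protocol gives neither, so both are assumed. With 9.9% in each full arm, the experimental risk after removing no-flap patients is 0.099 / (1 - f + f × RR). For f = 10% and RR = 2 this is 0.099 / 1.10 = 9.0%, a difference of -0.9 points. Differences, experimental minus control, in percentage points (negative favours the flap):

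| f | RR 0.5 | RR 1 | RR 2 | RR 3 |
|---|---|---|---|---|
| 5% | +0.25 | 0 | -0.5 | -0.9 |
| 10% | +0.5 | 0 | -0.9 | -1.65 |
| 20% | +1.1 | 0 | -1.65 | -2.8 |

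**5. The flap criterion, with a true effect.** Suppose the flap halves the risk and RR = 1. Patients with a flap have 9.9% / 2 = 4.95%. The full arm has 0.9 × 4.95 + 0.1 × 9.9 = 5.4% at f = 10%, and 0.8 × 4.95 + 0.2 × 9.9 = 5.9% at f = 20%. Exclusion makes the experimental arm look about 0.5 or 1.0 point better than the full randomised arm, even when suitability says nothing about prognosis.

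**The case against.** Several stronger readings are tempting and are not supported.

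- *That the protocol orders removal of no-flap patients.* It does not. Section {11b} is about the intervention and says nothing about analysis. It even lists a patient who refuses randomisation, so it is not a list of analysis exclusions. Section {20c} turns on complete data, not on receiving a flap. Removal is the probable joint reading with {11d} and {20a}, because the list puts no-flap patients beside withdrawals and losses.
- *That the bias is known to favour the flap.* The sign depends on a risk the protocol does not give: zero at RR 1, reversed below 1. The share may also be small. The Discussion reports 39 earlier cases and appears to say that insufficient flap length was not met, although those cases may have been selected.
- *That the exclusions fall on the experimental arm generally.* Only the flap criterion does. Bleeding, change of method, complications, withdrawal and loss can occur in either arm.
- *That unblinded staff may delete data at will.* Section {17b} does not say who asks or why. Withdrawal of consent is an equally possible purpose.
- *That harms and feasibility information vanish.* Adverse events are still recorded and reported ({22}), and reasons for discontinuation are monitored ({18b}). What is lost is their place in the randomised comparison.

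A substantive counter-argument also stands. In a non-inferiority trial, keeping experimental patients who never received the flap dilutes any difference and can make non-inferiority easier to show. An all-randomised analysis alone is therefore not enough. The shifts in step 4 are also small beside a 15% margin, so they do not by themselves show a changed conclusion.

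None of this touches the core: removal of drop-outs and fatal complications is explicit, and no all-randomised analysis is offered.

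**Conclusion.** The concern holds in limited form. Sections {11d}, {20a} and {20c} exclude randomised patients on post-allocation grounds, and the comparison that randomisation protects is given up. Read with {11b}, one further exclusion is probable and in practice specific to the experimental arm.

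The comparison can therefore be biased, plausibly towards the flap. Under the assumptions of no true effect, 9.9% risk and 5% to 20% without a flap, the flap criterion alone shifts the difference by between +1.1 and -2.8 percentage points for relative risks of 0.5 to 3. The wider exposure is the planned 20% loss, which exceeds the expected events on either reading of 144. The analysis set should be corrected before the data are analysed.

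**What to change.** - **Primary comparison ({11d}, {20a}, {20c}).** Replace the exclusion sentences and the complete-case rule with an analysis of every randomised patient in the allocated arm, including no-flap patients, conversions and deaths. Use RVF status to last contact, with death as a competing event. Leaving {20c} unchanged would undo the other edits.
- **Second analysis set.** Keep a protocol-adherent analysis alongside, and require both to support any non-inferiority conclusion.
- **Section {11b}.** State that stopping or modifying the allocated intervention does not remove a patient from follow-up or analysis.
- **Feasibility.** Report the proportion of the experimental arm without a usable flap as a result under section {7}.
- **Section {17b}.** Limit deletion of data to withdrawal of consent for data use.

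The cost is mainly wording and one additional analysis, plus some follow-up of patients who left the allocated intervention. The downside is some dilution of the flap effect, which is why the second analysis is kept.

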### Provisions for post-trial care {30}

At the end of the trial, participants will return to the care of their treating clinician to determine any further treatment as required.

### Outcomes {12}

#### The primary outcomes

The primary objective of this trial is to demonstrate the efficacy outcomes of the experimental group in preventing RVF. This includes monitoring the difference in incidence of RVF between the two groups.

#### Secondary outcomes

The occurrence time of postoperative RVF.The occurrence time of RVF after stoma closure.Postoperative complications, such as anastomotic leakage, chylous leakage, and intestinal obstruction.Postoperative serological test indexes, such as FSH, LH, E2, CEA, and CA199.Others about evaluating surgical methods, such as the duration of the operation, quality of life, abnormal discharge in the vagina.

The score of a functional assessment of cancer therapy (FACT) system will be used to evaluate the patient’s quality of life.

All data about the outcome will be collected according to the follow-up timepoint in Table 1. Measurement data between the two groups will be analyzed with the *t*-test and rank-sum test, while categorical data will be analyzed with *χ*^2^ test. The duration time will be recorded as mean ± standard deviation, and the incidence data will be recorded as median (first quartile, third quartile). The significance level used for statistical analysis will be two-sided with confidence intervals at the 95% level. All results will be applied to analyze the reliability of the new operation method, and to explore whether this new operation method will cause changes in the related complications, female hormones, affect the effect of the operation, and quality of life.

**Table 1 Tab1:** Schedule of enrolment, intervention, and assessments

Timepoint	Screening	Baseline	Intervention		Follow-up(months)											
			**Before**	**After**	**0**	**3**	**6**	**9**	**12**	**15**	**18**	**21**	**24**	**36**	**48**	**60**

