### Trial design {8}

This is a single-site parallel group RCT designed to explore the feasibility of packing with laparoscopic dislocated fat flap containing ovarian vascular pedicle anterior to the anastomotic stoma after rectal cancer surgery to prevent RVF. It will be implemented in Fujian Medical University Union Hospital from April 2020 to March 2023. Female patients with low and medium rectal cancer who are eligible will be randomly assigned to the experimental group or the control group in a 1:1 allocation ratio. The sample size should achieve the goal of non-inferiority. All patients will sign the informed consent form before they are enrolled in the trial (Additional file 1).

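### RVF timing has no method that uses women without a fistula, RVF incidence is to be summarised as a median, and the primary incidence has no time point

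*Protocol article*

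**What the plan says.** **Timing.** Under Secondary outcomes, the protocol article lists "The occurrence time of postoperative RVF" and, next to it, the time of RVF after stoma closure. The same section says "Measurement data between the two groups will be analyzed with the" t-test and rank-sum test, with chi-square for categorical data. Section {20a} repeats this ("measurement data between the two groups will be analyzed with the" same two tests). No censoring rule and no time-to-event method appears anywhere in the article.

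**Summaries.** Under Secondary outcomes: "The duration time will be recorded as mean ± standard deviation", and "the incidence data will be recorded as median (first quartile, third quartile".

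**Primary outcome.** The primary outcome is described thus: "This includes monitoring the difference in incidence of RVF between the two groups". Section {20a} plans to "determine the confidence interval for the difference in the efficacy of surgical methods in preventing rectovaginal fistula", at the two-sided 95% level. Neither section names a time. Table 1 marks RVF occurrence at months 3, 6, 9, 12, 15, 18, 21, 24, 36, 48 and 60 and singles out none of these 11 visits.

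**Who is analysed.** Section {11d} removes dropouts and patients with other fatal complications from the analyses. Section {20a} leaves out patients who drop out. Section {20c} analyses only patients for whom all data required by the protocol are present.

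**The concern.** There are three separate faults.

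1. Time to RVF exists only for women who develop RVF; for the others it is censored or precluded by death. Comparing observed times by t-test or rank-sum discards every woman in whom a fistula was avoided. The remaining subset is selected by the outcome that the flap is meant to change, so the comparison is no longer a randomised one. Time after stoma closure adds a second selection, because closure also happens after randomisation.
2. A median with quartiles carries no information about a yes/no outcome that affects about one woman in ten.
3. Without a horizon, the planned risk difference could be taken at month 3, month 60 or any visit between. Under the complete-case rule it is also undefined who counts as complete. Trial design {8} says "It will be implemented in Fujian Medical University Union Hospital from April 2020 to March 2023", and Sample size {14} and Trial status treat these dates as the recruitment window. At any one data cut, follow-up can therefore differ by up to about 36 months between women.

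At stake are two secondary outcomes that cannot show prevention, and a primary estimate whose value and denominator depend on a visit chosen later.

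**Working it through.** **Inputs from the document.** RVF incidence of 9.9% in both arms, 115 per group and 20% loss giving 144 (Sample size {14}); reported range 0.9% to 9.9% (Background {6a}); 39 uncontrolled flap cases without RVF over 3 to 14 months (Discussion). **Assumptions, not in the document:** flap-arm rates of 4.95%, 3%, 2% and 1%; RVF times exponential with mean 6 months.

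**The plan's own figure.** 115 / (1 − 0.20) = 143.75, so 144 reproduces and is a per-group number. The 115 itself does not follow from the stated non-inferiority inputs. With n = 2p(1 − p)(z₁₋α + z₀.₈)² / margin²:
- one-sided 0.025: 2 × 0.099 × 0.901 × (1.960 + 0.842)² / 0.15² gives 63 per group;
- one-sided 0.05: the same with 1.645 gives 50.

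That is a different matter. Here 115 is taken as given and enters only through the number of events.

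**Step 1: how many RVF times there are.** Expected number = 115 × rate; chance of no event = (1 − rate)^115.

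| RVF rate | Expected RVFs in 115 | Chance of none |
|---|---|---|
| 9.9% (planned, both arms) | 11.4 | negligible |
| 3% (assumed, flap arm) | 3.5 | 0.97^115 = 3% |
| 1% (assumed, flap arm) | 1.2 | 0.99^115 = 31% |

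On the plan's own assumption the timing test compares about 11 values with about 11. If the flap works it compares about 11 with 3 to 4, or with 1. With no flap-arm RVF it cannot be computed.

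**Step 2: whether the timing test responds to prevention.** Simulation with 115 per arm, 4,000 runs per scenario and the same time distribution in both arms. Timing tests use women with RVF only and are counted in runs with at least 2 RVFs in each arm.

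| Control vs flap rate | Runs with ≥ 2 RVFs in each arm | t-test rejects | Rank-sum rejects | Incidence comparison rejects (all runs) |
|---|---|---|---|---|
| 9.9% vs 4.95% | 98% | 4.2% | 4.3% | 31% |
| 9.9% vs 2% | 67% | 5.2% | 3.6% | 75% |
| 9.9% vs 0.9% | 29% | 5.8% | 2.9% | 92% |

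The timing tests stay near the nominal 5% or below it, however many fistulas are prevented. This follows from equal timing among women with RVF, and it is the point: prevention alone does not move these tests.

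**Step 3: median and quartiles of a yes/no outcome.** With 11 RVFs in 115 women, the ordered values are 104 zeros followed by 11 ones. The upper quartile lies at about the 86th value, so the summary is 0 (0, 0). With 1 RVF in 115 it is again 0 (0, 0), and with 28 in 115 (24.3%) still 0 (0, 0). The median is 0 for any incidence below 50%, and all three quartiles are 0 below about 25%.

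**Step 4: horizon.** Set side by side, the primary outcome and {20a} give a difference in incidence without a time, Table 1 gives 11 candidate times, and {20c} requires complete data without saying up to which visit. A woman followed without RVF to month 24 is complete for a month-12 or month-24 endpoint and incomplete for a month-60 one.

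**The case against.** - **The link to the t-test is inferred.** No sentence assigns RVF time to the t-test or rank-sum test, and the duration summarised by mean and standard deviation may be operating time, which is listed in the same section. This stands as a caution. The inference is still the natural one, since RVF time is a measured variable and no other method is offered. A statistical analysis plan that is not shown could add a time-to-event method, but the published text would still need correcting.
- **A reader might infer that the primary analysis measures no treatment effect.** The document does not support that. Section {20a} plans a 95% confidence interval for the between-group difference, and chi-square is given for categorical data. What is missing is the time to which the difference refers.
- **A reader might infer that short follow-up and early deaths count as free of RVF.** Sections {11d}, {20a} and {20c} point the other way: dropouts, incomplete cases and other fatal complications are excluded.
- **A reader might infer that the timing result could be reversed**, with flap-arm fistulas looking earlier because late ones were prevented. That needs selective prevention of late fistulas. No passage supports it, and the simulation did not test it.
- **The median wording is a local slip.** This is fair: {20a} does not tie the median to incidence, and no test uses it. It is a simple correction.

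**Conclusion.** The point holds in three parts. First, the methods stated for measured data, applied to RVF time, use only women with RVF: about 11 per arm at the planned 9.9% with 115 analysed per arm, and fewer in an effective flap arm. The comparison is not randomised, is insensitive to prevention, and cannot be done if the flap arm has no events. Second, median and quartiles for incidence give 0 (0, 0) at any rate the article cites. Third, the primary incidence has no time point among 11 visits from month 3 to month 60, so neither the planned confidence interval nor the complete-case population is fully defined.

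The event count of about 11 rests on the document's own figures. The 3 to 4 and 1 rest on assumed flap-arm rates, and the rejection rates on assumed exponential times that are equal in both arms. The first part also rests on the inference that RVF time is treated as measurement data.

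**What to change.** 1. Name one existing Table 1 visit as the horizon for primary RVF incidence. The investigators should choose it before results by arm are seen. Because an interim comparison is planned at 80–100 patients and 96 are already recruited, the amendment should state whether any such results have been seen. Report n/N (%) per arm with the risk difference and 95% confidence interval already planned in {20a}, and treat later visits as supportive.
2. Analyse time from surgery to RVF in all randomised women by cumulative incidence, with loss to follow-up censored and death as a competing event. Give a hazard ratio only if both arms have events.
3. Align the exclusion sentences in {11d}, {20a} and {20c} for this analysis; as they stand they contradict it.
4. Report time after stoma closure descriptively.
5. Delete the median (first quartile, third quartile) wording for incidence.

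**Cost.** A small protocol amendment, which under {25} means resubmission to the registry and renewed ethics approval. Table 1 has no row for the date of stoma closure; if the case report form does not record it, that date must be added. RVF occurrence and its time are already scheduled at every follow-up visit from month 3.

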#### Inclusion criteria

Patients who meet the following conditions will be included:Refer to the diagnostic and classification criteria for colorectal cancer of the American Joint Committee on Cancer (AJCC) and The Union for International Cancer Control (UICC) [9], seventh edition. The diagnosis of rectal cancer is confirmed with cTNM staging, T3–4NxM0.Female patients with ovarian failure after chemoradiotherapy or postmenopausal patients (serum FSH > 40U/L, LH > 20 IU/L, and E2 < 10–20 pg/mL).Received preoperative neoadjuvant chemoradiotherapy: radiotherapy regimen (long-range radiotherapy: DT50Gy/25F), chemotherapy regimen (XELOX regimen).Preoperative tumor distance to anal margin ≤ 7 cm.No other primary malignant tumor has been diagnosed.The clinical data are complete and prophylactic ileostomy is acceptable.The consent is signed.

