### Sample size {14}

Female patients with low and medium rectal cancer in the Department of Colorectal Surgery, Fujian Medical University Union Hospital, from April 2020 to March 2023 are selected as the research participants. It is assumed that the RVF of the study group is the same as that of the control group. According to previous research results and relevant literature reports, the incidence of RVF of the control group and the test group was set at 9.9%, the non-inferior margin value was set at 15%, the test level was set at 0.05, and the power was set at 0.8 [1, 2]. The sample size was calculated by SPSS24.0 software as follows: *N* = 115, and each group needed 115 people. We assume that 20% of patients would be lost to follow-up, and 144 would need to be enrolled.

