## Assignment of interventions: blinding

### Who will be blinded {17a}

Patients are not blinded. Caregivers are not blinded. Statisticians will not know the allocation.

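### The time of RVF after stoma closure is compared between arms only in women selected after randomisation; the estimate is biased if the flap alters closure and closure is related to later RVF risk

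*Protocol article*

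**What the plan says.** - Secondary outcomes, under Outcomes {12}, lists "The occurrence time of RVF after stoma closure" separately from the time of any RVF after the operation. Table 1 schedules it at every visit from month 3 to month 60.
- The Abstract (Methods) names it among the variables on which the participants will be compared, so a between-arm comparison is intended.
- The tests are fixed in the same section: "Measurement data between the two groups will be analyzed with the" t-test and rank-sum test, with chi-square for categorical data. Statistical methods {20a} repeats this.
- The stoma enters through the inclusion criteria: "The clinical data are complete and prophylactic ileostomy is acceptable". The article gives no rule for closing it and no expected closure rate, and Table 1 has no row for closure or its date.
- The protocol treats as open "whether this new operation method will cause changes in the related complications", and anastomotic leakage is one of the complications it lists.
- On blinding, {17a} states: "Patients are not blinded. Caregivers are not blinded".
- On the analysis set, {20c} states "We perform statistical analysis on the complete case" and {20a} states "Patient data that falls off will not be included in the analysis".

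**The concern.** A woman contributes a time to this outcome only if her ileostomy has been closed and an RVF follows. Randomisation makes the arms comparable at entry. It does not make the women who later reach closure comparable. If the flap reduces or increases leaks, one arm may send more women at high risk of a late fistula through to closure than the other. The difference then seen after closure reflects who was selected, even if the flap changes no woman's risk once she is closed.

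This is separate from the choice of test. A survival analysis that started the clock at closure would still compare two selected groups. At stake is the reading of one secondary result, which could appear to favour or disfavour the flap for the wrong reason.

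**Working it through.** The documents give no figure for this outcome, so there is none to reproduce. They supply only the arm size: 115/(1 − 0.20) = 143.75, which rounds up to the stated 144. Sample size {14} does not say whether 144 is per group or in total, so both readings are used: 144 per arm, and 144/2 = 72 per arm.

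**Assumed inputs (none is in the documents).**
- 30% of women are at high risk of late RVF.
- The risk of RVF after closure is 20% in high-risk women and 2% in the others, the same in both arms. The flap therefore has no effect on post-closure RVF in any woman.
- 98% of the other women are closed, in both arms.
- Closure is prevented in a fraction b of high-risk women. In the control arm b = 0.60; in the flap arm it varies.

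**Formulas.**
- Closed = 0.30(1 − b) + 0.70 × 0.98
- RVF after closure = 0.30(1 − b) × 0.20 + 0.70 × 0.98 × 0.02
- Risk among the closed = RVF after closure / closed

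**Results.**
- b = 0.60: closed 0.120 + 0.686 = 0.806; RVF 0.0240 + 0.0137 = 0.0377; risk 4.7%.
- b = 0.30: closed 0.210 + 0.686 = 0.896; RVF 0.0420 + 0.0137 = 0.0557; risk 6.2%.
- b = 0.10: closed 0.270 + 0.686 = 0.956; RVF 0.0540 + 0.0137 = 0.0677; risk 7.1%.

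Post-closure RVF is thus 3.8% to 6.8% of randomised women, which fits below the 9.9% total RVF assumed in {14}.

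Simulation (4,000 runs) gives the share of chi-square tests on post-closure RVF with p < 0.05:

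| Closure prevented, high-risk women (control / flap) | Risk among closed (control / flap) | False difference | 72 per arm | 144 per arm |
|---|---|---|---|---|
| 60% / 60% | 4.7% / 4.7% | 0 | 4.7% | 4.4% |
| 60% / 30% | 4.7% / 6.2% | +1.5 points | 5.2% | 7.9% |
| 60% / 10% | 4.7% / 7.1% | +2.4 points | 7.7% | 11.4% |

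Two further cases mark the limits. With 30% prevented in control and 60% in the flap arm, the false difference is −1.5 points, in the flap's favour. If both risk groups have the same post-closure risk (5%), unequal closure gives a difference of 0.

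**The listed outcome, a time.** Assume further that the mean time to RVF is 3 months in high-risk women and 9 months in the others. The mean among women with an event is then:
- b = 0.60: (0.0240 × 3 + 0.0137 × 9)/0.0377 = 5.2 months
- b = 0.30: (0.0420 × 3 + 0.0137 × 9)/0.0557 = 4.5 months
- b = 0.10: (0.0540 × 3 + 0.0137 × 9)/0.0677 = 4.2 months

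Against the control value of 5.2, the false shift is about −0.7 to −1.0 month. Expected events per arm are about 3 to 5 at 72 per arm (72 × 0.0377 = 2.7; 72 × 0.0677 = 4.9) and about 5 to 10 at 144. In the two unequal-closure scenarios the rank-sum test rejected in 1.6% and 2.5% of runs at 72 per arm, and in 4.4% and 5.7% at 144, counting runs with at least two events in each arm.

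**The case against.** The strongest case against is that the bias is conditional, small here and confined to a supporting outcome. Much of this stands.

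- **A reader might infer that a wholly neutral flap could look harmful or protective merely because fistulas before closure fall unevenly between the arms.** The calculation does not support that. When closure is prevented equally, the difference is 0 and the rejection rate stays at its nominal level. Uneven splits by chance are sampling noise. Bias needs the arms to differ in closure and closure to be related to later risk.
- **A reader might infer that a leak or fistula delays closure, and that clinicians who know the arm decide it.** This is reasonable, but the article does not say it. It gives no closure rule and names no decision-maker; {17a} says only that patients and caregivers are unblinded.
- **A reader might infer a raised false-positive rate for the listed outcome.** The rise in the table concerns the proportion with RVF after closure, whereas the article lists a time. For the time, rank-sum rejection stays at or near 5%.
- **A reader might infer from the complete-case rule that women never closed drop out of every analysis.** The article does not say that an outcome that cannot apply counts as missing.
- **An analysis plan, not shown, might set the population for this outcome.** It might, but the article already names the outcome, the between-arm comparison and the tests. Restricting the analysis to closed women is what creates the problem, so such a restriction would not repair it.

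The objection does not remove the core: a between-arm comparison is fixed in a subset defined by events after randomisation, and no other section restores the randomised groups. The blinded data collection in Data management {19} protects how outcomes are recorded, not who reaches closure.

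**Conclusion.** The point holds in conditional form. The comparison is not protected by randomisation, and its estimate is biased in either direction if the flap affects who is closed or when and closure is related to later RVF risk. Because the protocol itself asks whether the flap changes complications such as anastomotic leakage, unequal closure is a live possibility. It is not an established fact.

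The size rests entirely on assumed risk groups and closure rates: a false difference of about 1.5 to 2.4 percentage points in post-closure RVF, or about 0.7 to 1.0 month in its timing from a handful of events. The primary outcome and the RVF outcome timed from the operation are not conditioned on closure, so this does not threaten the trial's main conclusion.

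**What to change.** In Secondary outcomes and Statistical methods {20a}:
- Report RVF after stoma closure as description only, by arm and without a p-value. Show beside it, by arm, the number and dates of stoma closures and the reasons for non-closure.
- Rest the between-arm inference on RVF measured from surgery in all randomised women, using the timing outcome already listed. Women without an RVF must contribute their follow-up time, and death must be handled explicitly, for example as a competing event.
- Optionally, add the proportion with stoma closed and free of RVF at a fixed time from surgery. Every reason for non-closure must then be assigned in advance and the components shown.

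The rules in {11d}, {20a} and {20c} that remove drop-outs, fatal complications and incomplete cases need a matching edit, or an analysis of all randomised women cannot be done. No rule on when to close a stoma is needed or proposed.

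The cost is small. Follow-up visits already exist in Table 1. Closure dates and reasons must come from the case report form or hospital records, including for the 96 women already recruited. The post-closure result loses its formal test.
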